### **3. Trial Design**

#### **3.1 Design procedures**

This study is a single center, randomized, observer blind, placebo-controlled heterologous prime-boost immunization clinical trial, with “0-28 days” and “0-56 days” immunization regimens. The subjects are divided into two age groups, i.e. 18-59 years and 60 years and above.

Stage 1: According to the "0-28 days" regimen, sixty eligible subjects (30 in each age group) meeting the protocol requirements will be randomly assigned in a 2:1 ratio to receive a RBD-based protein subunit vaccine (CHO) or placebo (influenza vaccine).

Stage 2: According to the "0-56 days" regimen, sixty eligible subjects (30 in each age group) meeting the protocol requirements will be randomly assigned in a 2:1 ratio to receive a RBD-based protein subunit vaccine (CHO) or placebo (influenza vaccine).

Stage 3: For 0-28 days regimen and 0-56 days regimen, all participants receive a boost vaccination with ZF2001 at 4 months after the 1st boost dose.

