#### **3.2 Study Endpoints**

##### **3.2.1 Primary endpoints:**

- Incidence of solicited adverse events within 7 days after each booster vaccination.
- GMT of neutralizing antibodies against live SARS-CoV-2 virus at day 14 after each booster vaccination.

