### 3.4 Sample size calculation

Sample size:

Hypothesis: GMT of vaccine group is superior to that in the control group at day 28 after the booster vaccination.

The baseline GMT level before the booster immunization is expected to be about 1:20 ( $\log_{10}X=1.3$ ) after one dose of prime vaccination with Ad5 vectored COVID-19 vaccine. After the booster dose, GMT level in the vaccine group is estimated to reach 1:60 ( $\log_{10}X=1.78$ ), while the control group remains 1:20. Assume that the Standard Deviation is about 4 ( $\log_{10}X=0.6$ ), and the allocation ratio for the vaccine group and placebo group is 2:1, then the minimal sample size to provide 80% power calculated is 40 and 20, respectively.

In each regimen group, subjects are stratified to two sub-age groups: 18-59 years and 60 years or above.

Table 3. Sample size of each immunization regimen

| regimen   | Sub-age group     | sample size                |                       |
|-----------|-------------------|----------------------------|-----------------------|
|           |                   | Experimental vaccine group | Placebo control group |
| 0-28 days | 18-59 years       | 20                         | 10                    |
|           | 60 years or above | 20                         | 10                    |
| 0-56 days | 18-59 ages        | 20                         | 10                    |
|           | 60 years or above | 20                         | 10                    |
| Total     | —                 | 80                         | 40                    |

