### **5.8.3 Data statistics method**

During statistical analysis, first, the number of completed cases and drop-out cases should be checked. Then demographic and baseline characteristics of each group at enrollment should be analyzed to investigate intergroup comparability. Efficacy evaluation of vaccine includes the determination of evaluation indicators and intergroup comparison of efficacy. Safety evaluation includes the statistics of clinical ARs/AEs.

Participant elimination criteria: participants don't meet the inclusion criteria; data and information after vaccination are not followed up; information and data after randomization are seriously missing; participants meet exclusion criteria but are not withdrawn; participants receive wrong vaccination or

incorrect dose.

Safety analysis in this trial mainly includes descriptive analysis of the incidence of ARs/AEs.  $\chi^2$  test may be carried out for intergroup comparison, and Fisher's exact test may be performed if necessary. After immunization, the number of case-times and person-times of local AEs in the high-dose group will be calculated (with conventional calculation method). The number of person-times will be calculated based on the highest severity in both arms, and the number of case-times will be calculated based on the cumulative local AEs actually occurring at the vaccination site. Logarithmic transformation is required for analysis of immunogenicity indicator of antibody level which should be expressed as GMT, standard deviation, median, maximum and minimum and 95% confidence interval. Classification indicators will be compared between groups. Antibody seroconversion rate will be analyzed by  $\chi^2$  test and Fisher's exact test may be used if necessary. Study data at different time points will be analyzed with statistical analysis for repeated measurement data.

SAS 9.4 is adopted for all statistical analyses with two-sided test. The P value is directly calculated while carrying out Fisher's exact test when test statistics and corresponding P values are given, and in case of  $P \leq 0.05$ , the difference is statistically significant.

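### The only superiority hypothesis is at day 28, a secondary time point, while the primary GMT endpoint is day 14 after each of two boosters in two regimens, unranked and under a single P ≤ 0.05 rule

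*Protocol*

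**What the plan says.** - **Primary endpoint.** Section 3.2.1 lists "GMT of neutralizing antibodies against live SARS-CoV-2 virus at day 14 after each booster vaccination". The other primary item is solicited adverse events, and 5.8.3 handles safety mainly by description.
- **Regimens.** Section 3.1 describes a trial "with “0-28 days” and “0-56 days” immunization regimens". Each regimen has 60 participants randomised 2:1, so each contains its own vaccine-versus-control comparison. At the second booster, every participant in both regimens receives ZF2001.
- **Hypothesis.** Section 3.4 states one: "Hypothesis: GMT of vaccine group is superior to that in the control group at day 28 after the booster vaccination". It names neither the regimen nor which booster. Section 3.2.2 lists neutralising GMT at day 28 after the first booster as a secondary endpoint. After the second booster, the GMT time points are day 14 (primary) and month 6 (secondary).
- **Sample size.** Section 3.4 and its Table 3 give 40 vaccine and 20 control participants in each regimen for 80% power.
- **Test rule.** Section 5.8.3 says "SAS 9.4 is adopted for all statistical analyses with two-sided test", then, on P values, "in case of $P \leq 0.05$ , the difference is statistically significant". The protocol does not order the primary contrasts, split alpha between them, or say whether one success is enough.

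**The concern.** The protocol fixes three things that do not fit together: a hypothesis at one time point, a primary endpoint at another, and a sample size for a single test per regimen. The primary endpoint yields four day-14 vaccine-versus-control contrasts (two boosters in each of two regimens), and these can disagree. If the first-booster contrast reaches 0.05 in the 0-28 regimen but not in the 0-56 regimen, or the second-booster contrast succeeds where the first failed, the protocol does not say what has been shown. The day-28 result could also be presented as the confirmatory one, because it is the only one with a stated hypothesis.

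The two booster contrasts also ask different questions. After the first booster, the comparison is ZF2001 against influenza vaccine. After the second, it is two ZF2001 doses against influenza vaccine followed by one ZF2001 dose. The planning assumption in 3.4, a control group that stays at 1:20, can describe only the first.

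**Working it through.** **Reproducing the sample size.** Inputs from 3.4: log10 GMT 1.78 v 1.30, so a difference of 0.48; SD 0.6 on the log10 scale; allocation 2:1; power 80%. Two-sided testing at 0.05 comes from 5.8.3.

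- Normal approximation: control n = (1.960 + 0.842)² × (0.6² / 0.48²) × (1 + 1/2) = 7.85 × 1.5625 × 1.5 = 18.4, so 19 control and 38 vaccine.
- t-test: 38 v 19 gives 79.9%, so 40 v 20 is the smallest 2:1 size that reaches 80%. At 40 v 20 the noncentrality is 0.48 / (0.6 × √(1/20 + 1/40)) = 2.92 on 58 degrees of freedom, and power is 81.9%.
- One-sided 0.05 would need only 30 v 15, so it does not reproduce the stated size.

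The stated size is therefore the minimum for one unadjusted two-sided 0.05 test in each regimen.

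**False-positive rate if more than one contrast may carry the claim.** The regimens have different participants, so they are treated as independent. The two booster contrasts within a regimen share participants. The protocol gives no correlation ρ between them, so a range is shown. Let w be the probability that at least one of the two tests in a regimen is significant under the null (bivariate normal). Over both regimens the rate is 1 − (1 − w)².

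| ρ (assumed) | Either booster, one regimen (w) | Any of four contrasts |
|---|---|---|
| 0 | 9.75% | 18.5% |
| 0.5 | 9.1% | 17.3% |
| 0.8 | 7.8% | 15.0% |
| 0.9 | 7.0% | 13.6% |

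Checks at ρ = 0: 1 − 0.95² = 9.75% and 1 − 0.95⁴ = 18.5%. In the limit ρ = 1, the rates fall to 5% and 9.75%.

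**Power under possible remedies** (40 v 20, same effect and SD, t-test):

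- One test per regimen at 0.05: 81.9%, unchanged.
- Alpha split equally over two boosters (0.025 each): 73.1%. Restoring 80% would need about 46 v 23 per regimen (normal approximation).
- Holm across the two regimens, effect present in both: 0.731 + (0.819 − 0.731) × 0.731 = 79.6% for each regimen.
- Holm, effect present in one regimen only: essentially the 0.025 figure, 73.1%. The second Holm step adds only (0.819 − 0.731) × 0.025, or about 0.2 percentage points.

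**The case against.** The strongest objection is that multiplicity rules commonly sit in the statistical analysis plan. Section 5.7.4 refers to one, locked together with the database, and it is not at hand. That stands as far as it goes: a missing alpha rule alone would not be a finding. What remains is what the protocol itself states, namely a hypothesis that does not match its primary endpoint and a primary endpoint that names two unranked time points. A later plan would have to depart from one or the other.

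Second, 3.2.1 lists endpoints, not tests, and 5.8.3 specifies no between-group test for GMT beyond log transformation, confidence intervals and an unspecified repeated-measures analysis. The P ≤ 0.05 sentence can be read as a labelling convention. This is also fair, and it is why the error rates above are conditional on how the results are used.

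Third, the regimens have their own participants, controls, randomisation and sizing. They can reasonably be treated as two questions, each at 5%. Adjusting across them is a matter of preference, and the fix does not require it.

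A reader might go further in four ways that the document does not support:

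- **That no hypothesis is named at all.** Section 3.4 does name one; it is attached to a secondary time point.
- **That the trial's error rate is about 17%.** That figure needs a correlation near 0.5 and a rule that any one of four wins is success. Neither is stated.
- **That power is really 0.819² = 67.1%.** This holds only if both regimens must succeed, which the protocol never requires.
- **That dozens of secondary comparisons will yield several false positives.** This assumes each secondary summary is tested between arms and every null is true. The protocol specifies neither.

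**Conclusion.** The point holds as a mismatch and a lack of ranking within the protocol. The hypothesis in 3.4 (day 28, unspecified booster) and the primary endpoint in 3.2.1 (day 14, each booster, two regimens) must be reconciled, and one contrast per regimen must be named as deciding. The sample size supports exactly one unadjusted two-sided test per regimen.

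The size of the problem depends on the reading. It is 5% per regimen if only the first-booster contrast decides. It is 7.0% to 9.75% per regimen if either booster may, and 13.6% to 18.5% overall if any of the four may. The ranges assume a within-regimen correlation of 0.9 down to 0 and independence between regimens. The protocol does not choose among these readings, so none of the figures is the trial's stated error rate.

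**What to change.** In 3.4 and 5.8.3, state the deciding contrast as the ratio of neutralising GMT, ZF2001 to influenza vaccine, at day 14 after the first booster. Test it once in each regimen at two-sided 0.05, and make the superiority claim separately for each regimen. Restate the 3.4 hypothesis at day 14, and confirm that the assumed 1:60 v 1:20 and SD 0.6 are meant for that visit. Limit the blanket significance sentence in 5.8.3 to these two tests.

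Report the second-booster contrast, the secondary endpoints and the age-group results as estimates with 95% confidence intervals. Alternatively, test the second booster within a regimen only after the first has succeeded there, which keeps the error for that pair at 5%.

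If the sponsor wants one trial-level claim that either regimen can support, use Holm across the two regimens. Restate power as 79.6% per regimen, or about 73% if only one regimen has the effect.

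The main proposal costs wording only: no extra participants or samples, and power stays at 81.9% per regimen. The downside is that second-booster and secondary results lose the unqualified label "the difference is statistically significant". Because the Document History gives the antibody levels at day 14 after the first booster as the reason for version 1.3, the amendment should be dated and should record what was known by arm when it was made.

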## **6. Monitoring of Clinical Trial**

### **6.1 Quality assurance and quality control**

Carry out on-site quality control in strict accordance with the relevant requirements of Good Clinical Practice (GCP).

Investigators in some positions are qualified as physicians or above. Prior to the clinical trial, they will be trained in the clinical protocol and all trial procedures, including information about the trial vaccine, procedures for obtaining informed consent, operating procedures for each position, and procedures for reporting adverse reactions/events.

The data of each subject is reviewed at each stage of the clinical trial to ensure that the content of the clinical trial meets the requirements of the protocol and that the obtained data are complete and reliable.

The quality controller controls the whole process of the clinical trial.

All the work on site are carried out strictly in accordance with the clinical trial field operation manual.

Each subject records the "*Diary Card*" by themselves, follows up and retrospectively investigates by the researcher, and reviews and guides the filling in of the "*Diary Card*".

The quality controller shall conduct a comprehensive check on the original data, and after training, a special person shall enter the data of eCRF. The double entry method shall be adopted and completed by two people independently.

Calibration or standardization of the instruments used in this clinical trial.

## **6.2 Modification of clinical protocol**

After this plan is approved by the Ethics Committee, if there is any major modification in the implementation process, it shall be reported to the Ethics Committee for approval before it can be implemented. The investigators shall not execute any deviation or change without the consent of the Sponsor and prior review and written approval of the Ethics Committee (EC).

Any changes to the scheme, whether material or non-material, are required to be in writing. EC approval is required to identify substantive protocol changes that would affect the safety of subjects, the scope of the study, or the scientific quality of the study.

## **6.3 Scheme deviation**

The investigators shall carry out the clinical trial according to protocol approved by the ethics committee and the provisions of GCP. During the trial, the researcher shall not deviate from the protocol unless the harm to the subjects is eliminated.

The research center shall record all protocol deviations in the original data of subjects, including but not limited to the occurrence time of protocol deviation, discovery time, event description and measures, etc. In case of serious protocol deviations, the main researchers should be informed in time and report to the IEC.

## **6.4 Confidentiality**

The sponsor, investigators, IEC, or a fully authorized representative of regulatory authority should have the right to obtain data related to the clinical trial, but relevant content cannot be used for any other clinical trials, nor can it be disclosed to any other individuals or entities.

Investigators must sign a confidentiality agreement to confirm that he/she knows and agrees to hold the information of this study confidential.

Investigators and other study personnel should keep all information provided by the sponsor and all data/information generated at the study site (except for medical records of participants) confidential. Such information and data should not be used for any purposes other than the study. This restriction does not apply to: (1) study information is not disclosed because of violations by investigators and researchers; (2) study information is disclosed only to the IRB/IEC for the purpose of study evaluation; (3) study information is disclosed to provide appropriate medical assistance to participants.

## **7. Schedules**

In this study, it will take about 10 months from the preparation before initiating this study to the completion of the summary report. The schedule of clinical trial is shown as follows (for reference only):

| Implementation process of clinical trial                                    | Proposed duration |
|-----------------------------------------------------------------------------|-------------------|
| 1. Preparation before clinical trial                                        | 18 days           |
| 2. IEC Review Approval                                                      | 3 days            |
| 3. Recruitment and enrollment of the first participant                      | 1 month           |
| 4. 28-day visit after the last participant completes the last dose          |                   |
| 5. First analysis                                                           | 1 month           |
| 6. First analysis report                                                    |                   |
| 7. 6-month visit after the last participant completes the last immunization | 6 months          |
| 8. Final analysis                                                           | 1 month           |
| 9. Summary Report                                                           |                   |

## 8. Ethical Approval

### 8.1 Ethical Review and Approval

The PI should submit the clinical trial protocol and all necessary additional documents to the IEC for initial review:

- Clinical study protocol (indicated with version No. / date)
- Informed Consent Form (indicated with version No./date)
- Participant recruitment materials (indicated with version No. / date)
- Diary card (indicated with version No. / date)
- Contact card (indicated with version No. / date)
- Vaccination Visit Record (indicated with version No./date)
- PI's CV
- Drug clinical trial approval from the NMPA

After the above study documents are reviewed and approved by the IEC, a written approval certificate will be issued to the investigators.

### 8.2 Follow-up Review

Whether the methods for inclusion of participants and the information provided to participants are complete and understandable; whether the methods for obtaining informed consent are appropriate; whether SAEs are reported timely; and whether timely medical treatment can be provided for the SAE related to inoculation with the candidate vaccine.

During the whole trial, the IEC should supervise whether the risk-benefit ratio of the study is increased and whether the rights and interests of participants are effectively protected.

### **8.3 Potential risks and minimization of risks**

#### **8.3.1 Benefits and risks**

It is expected that participants in this program will likely gain an improved level of immune response against SARS-CoV-2 from a booster dose of COVID-inactivated vaccine or immune protection against influenza viruses from a booster dose of influenza vaccine. Mass vaccinations of both inactivated and influenza vaccines have demonstrated good safety, so no significant increase in safety risk is expected with an additional dose of vaccine. Participants in this clinical trial will not need to pay for the inoculation with investigational vaccines. Participants in this trial are provided with reasonable transportation fee, charge for loss of working time, blood collection compensation and nutrition fee. During participating in this clinical trial, participants will receive one dose of inactivated COVID-19 vaccine or influenza vaccine. At the same time, injection of vaccines may cause some ARs. Common ARs of vaccination include: pyrexia, injection site tenderness, redness and swelling. Generally, the AEs will be alleviated within 3 - 5 days after occurrence.

#### **8.3.2 Vaccination**

Qualified inoculation consumables will be purchased, and aseptic inoculation will be performed in strict accordance with standard method to avoid AEs caused by improper inoculation or inoculation error.

If a participant experiences a grade 3 or above AR during the safety observation period, or experiences a SAE related or possibly related to the candidate vaccine, he/she should be able to receive timely medical treatment, and if necessary, the “green channel for medical treatment” should be immediately initiated for emergency treatment.

#### **8.3.3 Blood specimen collection**

After qualification review by the PI, the experienced nursing staff will be employed to collect venous blood samples after training as per the specified procedures to minimize pains or risks (including pain and less chance of venipuncture site infection) from which the participants suffered.
